**Fig. 1 Fig1:**
[figure not shown]
APPEAL Trial Schemata

### Intervention

Intervention components and materials to support behaviour change are underpinned by the Behaviour Change Wheel theoretical framework and the Behaviour Change Technique Taxonomy (version 1) [18, 19] in line with the Medical Research Council’s guidance for developing and evaluating complex interventions (https://www.bmj.com/content/374/bmj.n2061).

Due to strict COVID-19 policies at NHS sites, midwife training will be provided via online interactive video-conferencing with small groups of midwives. Two research midwives will lead and facilitate initial training sessions lasting approximately 2 h. Training handbooks will be sent to intervention cluster midwives before their training. The training package will include an interactive session with vignettes and role-play to enable midwives to raise and discuss the importance of a healthy pelvic floor, benefits of performance of PFME to prevent UI, and a video of how to teach women about PFME. Information is presented on pelvic floor muscle anatomy and function; muscle exercise training principles (physiology), a stepped approach to assessing and teaching the correct muscle contraction, setting an individualised PFME training programme, information on how to screen for serious incontinence problems and criteria for referral.

Following training, midwives will initially introduce the topic of pelvic floor health at the antenatal ‘booking’ appointment or as early as possible after this. At this appointment the midwife will explain to the woman that she will receive a resource pack to help her perform PFME. Each resource pack will include an APPEAL leaflet with PFME information, a link to APPEAL developed videos, a card with links to recommended Apps to download to support PFME performance, and some promotional items (e.g. APPEAL logo stickers) to use as reminders. Women will be asked at all subsequent antenatal appointments about PFME progress (with adaptation of personalised PFME training programme where necessary) and any problems with PFME or UI symptoms.

Each intervention cluster will include a midwife ‘champion’ from the team who will receive additional training on how to support and manage women whose UI symptoms may be more severe or giving cause for concern, including appropriate referral pathways. Champions will also provide reminders and advice for midwives in their team. Midwives will be given 2 to 3 months (depending on date of their training) to practice implementing the PFME intervention into their routine care.

### Outcomes

The primary outcome is feasibility of undertaking a definitive future trial which we will assess in the following ways:Questionnaire return rates from women who give birth over a pre-selected 1-month period at 10–12 weeks postpartum overall and across trial armsPrevalence of UI at 10–12 weeks using the ICIQ-UI SF [20], and faecal incontinence at 10–12 weeks using the Revised Faecal Incontinence Scale [21]Women’s practice of PFME, their adherence and confidence using self-efficacy [22] and Exercise Adherence Rating Scales [23]

Secondary outcomes willAssess if the intervention can be implemented by midwives as part of routine antenatal careAssess midwife support for PFME in both trial arms from responses in women’s 10–12-week postpartum questionnaire to assess possible intervention contamination in the control clustersAssess women’s experiences in both trial arms of midwifery advice and support to perform PFME during pregnancy

The following progression criteria should be met to inform progression to a full RCT:Questionnaire return rate from women across trial arms is not likely to result in substantial bias, as indicated by either a high overall return rate and/or that women who return questionnaires in both trial arms have similar baseline characteristicsWomen’s self-reported adherence to performing PFME is higher among those in intervention clusters than in controlsMidwife support for PFME is reported as greater by women in the intervention than the control clusters

We have decided not to quantify particular progression criteria because the decision will be made based on a combination of criteria findings. The research team would seek the advice of the Trial Steering Committee (TSC) about progression to full trial when information on the above criteria has been obtained.

### Study procedures

#### Consent process

At their first postnatal contact, women in both trial arms who give birth over a pre-selected 1-month period will be informed by their midwife that they will receive a questionnaire and cover letter (comprising a short Patient Information Sheet) at 10**–**12 weeks postpartum. As the study involves low risk for participants, this approach complies with Health Research Authority guidance, section 2.5 on ‘applying a proportionate approach to the process of seeking consent’ [24]. All women who received antenatal care in the trial clusters with be included, but Trust Research Midwives will exclude women who experienced a stillbirth or neonatal death, those whose infants were taken into care due to safeguarding concerns and women with a current severe mental health problem, providing these data are available in the woman’s maternity records.

Women’s consent for their data to be used will comprise completion and return of their questionnaire. The cover letter will clearly state that by completing the questionnaire women agree to allow their responses to be used in the study. The letter will also ask the woman for permission for a Research Midwife from the study maternity unit to obtain relevant data items including socio-demographic characteristics, labour and birth outcomes and infant birth data from their maternity notes. The letter will stress that participation is voluntary with patient identifiers only accessible to Research Midwives at the study site. The letter will also ask if women would be prepared to provide their contact details for a member of the research team to contact them to arrange a short interview about their experiences of midwifery advice and support for PFME in pregnancy.

To reach women who do not read English as a first language, letters and questionnaires will be translated into the five other most commonly spoken languages at our study sites; Urdu, Pashto, Romanian, Polish, and Arabic. As not all outcome measures have been translated and validated in these languages, a shortened version of the questionnaire will be sent in these cases.

Permission to recruit midwifery teams was provided early in the trial set-up by heads of midwifery and community midwifery matrons at each NHS site.

#### Randomisation

Midwifery community-based teams (clusters) will be randomised in a 1:1 ratio to standard care only or standard care plus intervention. A minimisation algorithm implemented in Microsoft Excel by the study statistician will be used to ensure approximate balance over the following variables:Midwifery team size defined by number of births (≤median monthly bookings vs >median monthly bookings)NHS maternity unit

A ‘random element’ will be included in the minimisation algorithm, so that each cluster has a probability of being randomised to the opposite treatment that they would have otherwise received.

Blinding of midwives providing care will not be possible due to the nature of the intervention. Women receiving antenatal care will not explicitly be blinded but the PFME support they experience will be the usual care provided by their midwives. Those responsible for conducting the trial analysis (but not the process evaluation) will be blind to allocation.

#### Participant identification

Research Midwives employed by the NHS maternity units will work through the records of women who give birth under the care of the community midwifery-teams (clusters) during the pre-defined sample month and obtain their hospital number, name and address. Each woman will be allocated a unique study number to link their de-identified data from their questionnaires and maternity records prior to being entered onto a bespoke study database hosted by the local Clinical Trials Unit.

#### Women’s questionnaires at 10–12 weeks

The questionnaire pack will include a request to return the completed questionnaire to the unit Research Midwife in a pre-paid self-addressed envelope. A £10 voucher will be given to ‘thank’ women who return completed questionnaires. Table 2 shows data collection processes and timing.

Responses from completed questionnaires will be entered by a Research Midwife employed by the NHS maternity unit. The Research Midwives will provide a list of the hospital/NHS numbers of the women who grant permission for their maternity records to be accessed to their local IT Department to obtain information on:Woman’s age, ethnicity, parity, onset of labour (spontaneous or induced), mode of birth (spontaneous vaginal, instrumental, caesarean section), anaesthetic/analgesia used, perineal trauma, episiotomy, and duration of active second stage.Baby’s gestation at birth, birthweight, and head circumference.

**Table 2 Tab2:** APPEAL data collection process and timing

Outcome/data	Timing of data capture	Process
Midwifery team characteristics (clusters); midwife experience of trial processes	Various times throughout the cluster trial process	Number of births per team, number and grades of midwives per team and team location, number of women/births per team from NHS trust managers/community-team leads. Interviews with individual midwives in both study arms.
Health outcomes & PFME performance	Questionnaire follow up of all women in participating clusters at 10-12 weeks postpartum.	Overseen by local NHS trust Research Midwives. If no response to initial follow up, questionnaire resent. If no response after a further two weeks, other options will include sending a text message reminder
Data from women’s maternity records	On return of consent in women’s questionnaire.	Extracted by local trust Research Midwives from maternity records.
Data from telephone/online interviews with women from both trial arms	Interviews with 10-15 women from each trial arm	A sample of up to 30 women who agreed to be approached. Interviews to qualitatively explore their experiences of receiving (or not) information and advice about doing PFME during pregnancy; and to explore any possible contamination between arms.
Intervention cluster midwives’ views of training	Questionnaire to all midwives attending training, at start & end of the training session. On completing training roll-out in intervention clusters. Up to 15 midwives (including champions).	To evaluate the acceptability and effect on confidence of the training. Purposive sampling to represent cluster site/size. Telephone/online interviews during the practice month to assess acceptability, fidelity to intervention.
APPEAL midwives’ views of implementation of the intervention	Prior to completion of roll-out. All midwives in intervention clusters	Questionnaire to explore how midwives administered the intervention in practice, how often PFME were discussed with women at routine AN contacts, barriers and facilitators to implementation
APPEAL midwife champions views of role supporting roll-out and implementation of training intervention	On completion of intervention roll-out.	The APPEAL champions included in the aforementioned intervention cluster interviews. Telephone/online interviews to assess acceptability, fidelity to intervention pertaining to the champion role.
Midwives’ views on acceptability of the intervention/standard PFME advice (intervention and control clusters) and study processes (intervention and control midwives)	Interviews with up to 15 midwives from each trial arm.	Purposive sampling to represent cluster site/size. Telephone/online interviews to assess acceptability, fidelity to intervention (intervention) and potential contamination (control).

#### Women’s interviews

Women who agree to be approached will be purposively sampled from both trial arms based on their midwife team and location and invited to take part in one-to-one telephone or online audio interviews (using a secure web-based platform, i.e. Zoom). Up to 15 women from each arm will be interviewed.

Interviews will explore their views of doing PFME during pregnancy, whether they experienced incontinence and what support or advice they received from midwives or other health care providers. They will be asked about their current continence status, practice of PFME and if they have heard anything about the APPEAL study to enable the researchers to further estimate the level of any cross contamination from the intervention groups. Interviews will take place after the women have completed the 10**–**12-week questionnaire.

#### Participant withdrawal

A letter included with the 10–12-week questionnaire will make clear that women are under no obligation to participate. If a request to withdraw data is received after initial analysis their data will not be included in further analysis

#### Midwife pre- and post-training questionnaires

All community midwives from intervention clusters will be asked to complete a pre and post-training questionnaire immediately after their training session. They will be provided with a link during the session to complete the questionnaires online (using REDCap). Collected data will be pseudo-anonymised.

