#### Statistical analysis

A separate Statistical Analysis Plan will be produced to provide a comprehensive description of planned statistical analyses. We provide an overall summary of the proposed analysis here. The primary comparison groups are women in clusters allocated to intervention versus women in clusters allocated to standard care. In the first instance, all statistical analyses will be based on the intention to treat principle. Data analysis will be descriptive and mainly focus on confidence interval estimation, with no hypothesis testing. The assessment of missing data is an outcome measure of this feasibility and pilot trial.

We will report numbers contributing and numbers missing for all variables and descriptive statistics for all outcomes. Analysis methods will be chosen according to the data type of the outcome under investigation, in brief:Continuous endpoints (e.g. confidence scores elicited on a range 0**–**32): These data will be summarised using means and standard deviations, by armCategorical (dichotomous) endpoints (e.g. experience of UI in the past 4 weeks): The number of participants and percentages experiencing the event will be summarised by arm

For all total scores and dichotomous feasibility outcomes (e.g. proportion of women returning questionnaires) summary measures and 95% confidence intervals per trial arm will be estimated using a cluster level analysis, the *t*-distribution with df = *K*-1 and appropriate transformation where necessary (and weighting if there is variation in cluster sizes). This approach will appropriately allow for the clustered nature of the trial.

Quantitative data from intervention cluster midwives pre- and post-training session and intervention implementation questionnaires will be summarised using descriptive statistics and where appropriate inferential analysis undertaken using repeated measures statistical tests.

The final dataset will be available to members of the Trial Management and co-applicant group who need access to the data to undertake the final analyses.

Requests for access to data from the APPEAL trial should be addressed to [contact]. Anonymised individual participant data collected during the trial will be available with no end date. All proposals requesting data access will need to specify how the data will be used, and will need the approval of the trial management group prior to data release.

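### The midwives' pre-training questionnaire is placed after the training session in the text but at its start in Table 2; the two must be aligned so that a true baseline is collected.

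*Protocol article*

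**What the plan says.** Three places in the protocol article bear on this point.

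- **Midwife pre- and post-training questionnaires.** Community midwives from the intervention clusters "will be asked to complete a pre and post-training questionnaire immediately after their training session". On delivery, the section adds: "They will be provided with a link during the session to complete the questionnaires online".
- **Table 2 (under Women's questionnaires at 10–12 weeks), row on intervention cluster midwives' views of training.** The timing entry is "Questionnaire to all midwives attending training, at start & end of the training session". The stated purpose is "To evaluate the acceptability and effect on confidence of the training".
- **Statistical analysis.** The midwives' questionnaire results are to be reported descriptively, with a further provision: "where appropriate inferential analysis undertaken using repeated measures statistical tests". Earlier, the same section says: "Data analysis will be descriptive and mainly focus on confidence interval estimation, with no hypothesis testing".

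**The concern.** The text and the table describe the same instrument, given to the same midwives around the same session, yet they place the first measurement at different times. When a baseline is taken is a data-collection procedure. The article states it twice and inconsistently, so this is not a detail left to the statistical analysis plan.

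An effect of training on confidence is read from the change between two ratings. If the first is given after the session, the midwife is recalling how confident she was, having just learned what the task involves. Her standard for judging confidence may have moved (response shift), and she may want to show that the session helped. The resulting change is a retrospective self-assessment, which is a different quantity from a before-and-after change. If some sessions followed the text and others the table, the pooled change would mix the two. The loss is also permanent, because an untrained rating cannot be obtained from a midwife once she is trained.

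A second, lesser matter is that the Statistical analysis section excludes hypothesis testing and later allows repeated measures tests on these midwife data, without saying how the two statements fit together.

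**Working it through.** No arithmetic applies. The article gives no number of midwives, score scale, expected change or precision target for these questionnaires. The check is a comparison of the wording.

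**Timing**

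| Item | Midwife questionnaire section | Table 2 |
|---|---|---|
| Who | Community midwives in intervention clusters | Midwives attending training |
| First questionnaire | Immediately after the session | At the start |
| Second questionnaire | Immediately after the session | At the end |
| Delivery | Online, by a link given during the session | Not stated |
| Purpose | Not stated | Acceptability, and effect on confidence |

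1. The respondents are the same: Table 2's row concerns intervention cluster midwives, and only intervention clusters are trained.
2. The second questionnaire is placed consistently, since the end of the session and immediately after it are practically the same moment.
3. The first questionnaire is not. One place puts it before the teaching and the other after it. The Intervention section gives the initial session as about 2 hours, so the two timings are separated by the whole of the training being evaluated.
4. The delivery sentence does not settle the matter. A link given during the session could be given at its opening or its close, and one sentence covers both questionnaires.
5. The purpose in Table 2 needs a rating unaffected by the training. Only Table 2's timing supplies one.

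**Testing**

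1. The exclusion of hypothesis testing comes in the opening paragraph of Statistical analysis. That paragraph also says: "The primary comparison groups are women in clusters allocated to intervention versus women in clusters allocated to standard care".
2. The midwife questionnaires have their own later paragraph and method. The pre- and post-training pair goes only to intervention midwives, so there is no between-arm comparison of it to test.
3. The repeated measures tests are conditional: they apply only where appropriate.
4. No sentence limits the exclusion to women's outcomes or exempts the midwife data.

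Steps 1 to 3 favour a narrow reading of the exclusion, and step 4 leaves it unstated. This is an ambiguity of scope, not a firm contradiction.

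**The case against.** The strongest reply is that the timing conflict is a slip of wording. The section's heading, the link given during the session, the reference in Statistical analysis to data from before and after training, and Table 2, whose job is to set out timing, all fit an ordinary before-and-after design. Only one phrase does not, and it may have been meant to apply to the post-training questionnaire alone. Nothing in the article describes a retrospective baseline as a deliberate choice. This stands as an account of what was probably intended, and it is why the point is minor. It does not remove the conflict, because staff working from that section alone would collect the baseline too late.

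Three stronger readings are tempting, and the article supports none of them.

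- **That the confidence result will be uninterpretable.** This follows only if the text is applied in preference to Table 2, and the article does not show that it will be.
- **That the plan breaks its own rule against testing.** The rule sits in a paragraph built around women in the two arms, and the midwife tests are conditional and separately described. The most that can be said is that the scope should be stated.
- **That the midwife analysis ignores clustering and so overstates precision.** Midwives do work in teams and are trained in small groups. But the article names only a family of methods, does not rule out allowing for team or training group, and defers the full description to a separate statistical analysis plan. It gives neither the number of midwives per team nor an intracluster correlation for their scores, so any inflation figure would rest on invented inputs.

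**Conclusion.** The timing conflict is real and certain as written: the midwife questionnaire section and Table 2 cannot both be followed for the pre-training questionnaire. If the section's wording is applied, the baseline becomes retrospective and a true one is lost.

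Severity is minor. The training questionnaires are process-evaluation data. Change in midwives' confidence is not among the primary or secondary outcomes or the progression criteria in the Outcomes section, and no sample size or trial estimate depends on it. Table 1 does list acceptability of the training and revision of the training package as objectives, so the evaluation has some use, but that table does not name a change in confidence.

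The size of any bias cannot be stated from the article. The conclusion assumes only that the two places describe the same questionnaires, which the shared respondents and the shared session make clear. The testing matter is an optional clarification and does not add to the severity.

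**What to change.** **Main change.** Amend the midwife questionnaire section to match Table 2: the pre-training questionnaire is completed online at the start of the session, before any teaching, and the post-training questionnaire at the end. Give the link at the opening of the session so that this is possible. If a retrospective rating was in fact intended, both places should say so and the result should be labelled as such. If sessions have already been held, the report should state when the first questionnaire was completed at each.

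**Optional clarification in Statistical analysis.** Either limit the exclusion of hypothesis testing to the between-arm comparison of women's outcomes, or replace the repeated measures tests on the pre- and post-training scores with a mean paired change and its 95% confidence interval. The second option is in keeping with the section's emphasis on estimation.

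**Cost.** One sentence for the timing, one for the optional clarification, and a few minutes at the start of each session. The sample size, the outcomes and the progression criteria are unchanged.
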